### Trial design {8}

This trial is a double-blinded placebo controlled cRCT with two arms. A total of 56 clusters will be randomly assigned, in a 1:1 ratio, to one of the two arms to receive the intervention or the placebo control. The intervention is a Mossie-GO™ device, containing a transfluthrin-treated disc which sits above a fan powered by solar energy (Fig. 1). The control arm will receive the Mossie-GO™ device with an identical looking disc with no active ingredient. All eligible, consenting households will receive a single Mossie-GO™ device with 5 W solar panel, and discs will be replaced at monthly intervals. The device requires 2 h charging time during the day and should be switched on in the evening and placed in the room where the child ≤ 5 years of age sleeps. If multiple children ≤ 5 years of age sleep in different locations, one location should be selected. If there are no children ≤ 5 years of age within the household, the Mossie-GO™ device can be placed in an alternative sleeping room.

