### Outcomes {12}

The primary outcome measured in this study will be the average reduction in malaria infection prevalence in children ≤ 5 years of age from baseline to month 12, as measured by RDT and microscopy. Secondary outcome measures include:
CDC light trap indoor density for anophelines and by anopheline species, as measured by light trap collections from 7 pm to 7 am on a 6 monthly basis. Change in mosquito density at baseline and month 12 between arms will be analysed by negative binomial regression with a random effect for study cluster.Anopheline-human contact (indoor and outdoor) using human biting rate (HBR) as an indicator for all anophelines and by anopheline species, as measured by HLC during 6-h intervals on a 6-monthly basis. Change in HBR at baseline and month 12 between arms will be analysed by negative binomial regression with a random effect for study cluster.Anopheline infectivity using sporozoite rate as an indicator for all anopheline and by anopheline species, as measured by laboratory detection of sporozoites in mosquito heads and thoraces from a subsample of anophelines collected during CDC light trap and HLC collections.Insecticide resistance, as measured by WHO tube test bioassay, during the intervention phase. Confirmed resistance, possible resistance and susceptibility will be calculated through evaluating knockdown and mortality rates.Subject behaviour and household features related to exposure to malaria and use of existing control tools, as measured by quantitative and qualitative surveys on a 6-monthly basis. Survey outputs will be summarised using basic statistics.Concentration of transfluthrin in air over the duration of an evening’s use or the Mossie-GO™ and the impact of indoor temperature on the concentration, as measured by air sampling at months 9 and 12. Mean concentration will be compared between arms.Acceptability of Mossie-GO™ in these communities, as measured be quantitative and qualitative surveys at 6 and 12 months and FGDs at 12 months. Outputs will be summarised using basic statistics and thematic analysis.Safety of intervention through monitoring of AEs and SAEs. Measured actively and passively throughout the duration of the study and total number of events and type of events will be compared between study arms.

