## Assignment of interventions: allocation

### Sequence generation {16a}

All randomisation procedures will take place electronically. Treatment and control will be assigned as blinded, variables A and B, by the trial data manager and details of this assignment will be recorded in a sealed envelope and will not be shared with or accessible to any other team members.

The unit of randomisation is a cluster, corresponding approximately to villages within the study area. Clusters will be randomly assigned to two study arms, control and treatment intervention, using a computer-assisted constrained randomisation approach, facilitated by R [19]. To ensure adequate and feasible sampling, cluster selection will be restricted based on population size and population stability (Appendix Table 1). To reduce the impact of confounding factors, clusters will be stratified by land type (urban or rural) and study district, ensuring equal representation across both study arms. No significant inter-cluster variation was identified, meaning household selection within clusters will proceed as simple random sampling without blocking. This randomisation procedure involves generating 1000 unique sets of random treatment assignments. In each cycle, the differences in treatments allocated between district and land type strata will be assessed and the iteration with the least disparity, considered the most well-balanced iteration, will be selected as the final scheme for assigning treatments. Additional confounding factors will be factored into the statistical analysis (Appendix Table 2).

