### Implementation {16c}

The distribution of the intervention will occur immediately following baseline data collection, and thus verification of underlying assumptions of study power (prevalence and CV) will not be verified prior to distribution. Analysis of baseline data will take place prior to the first round of intervention data collection, providing an opportunity to revise sample sizes if necessary. Within a cluster, all consented households with a child ≤ 5 years of age will receive a device regardless of whether they are randomly selected for sampling at the baseline time point. Where spare Mossie-GO™ devices are available, households without a child ≤ 5 years of age will also be given a device. As per the manufacturer’s guidance, the device requires 2 h charging time during the day and should be switched on in the evening and placed in the room with the child ≤ 5 years of age. If multiple children ≤ 5 years of age sleep in different locations, one location should be selected. If there are no children ≤ 5 years of age within the household, the Mossie-GO™ device can be placed in an alternative sleeping room. Trained VHTs and data collectors will be responsible for deployment of the product and monthly refill/disposal of the discs at monthly intervals within the sample populations to ensure adherence. Reviews of device use will be conducted to inform any retraining requirements.

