## Appendix

**Table 1 Tab1:** Restricting factors for the selection of villages as study clusters, prior to the assignment of clusters to treatment arms

Confounding factor	Explanation
Household population size	Clusters were restricted to those with more than 109 households with children ≤ 5 years of age and no more than 245 total households. This ensured a sufficient sample size per time point while maintaining feasibility based on intervention resources
Population stability	Villages with significant seasonal population shifts, such as fishing communities, were considered separately to account for fluctuations at different time points (every six months)

**Table 2 Tab2:** Factors identified as potential cluster-level confounders. Only land type and study district were controlled for during random allocation, as detailed below

Confounding factor	Explanation
District	The study area spans two districts, Jinja and Buikwe, each governed independently. Districts were included as stratification factors
Socio-economic factors	Land type (urban/rural) was used as a proxy for socio-economic variation between clusters. Additional socio-economic data will be collected in household surveys for post-hoc analysis
Environmental heterogeneity	Spatial data on altitude and proximity to large water sources was unavailable before allocation of clusters. Preliminary assessments indicated that altitude variation was evenly distributed across the study area. These factors will be included in the final statistical analysis
Malaria interventions	Nationally distributed interventions, such as ITNs and IRS, were assumed to be homogeneously available across clusters. Household surveys will collect additional data on bed net usage for further analysis

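### The safety comparison is set on event totals per arm, although the allocation does not constrain how many households hold a device in each arm

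*Protocol article*

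**What the plan says.** All places are in the protocol article.

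- **Metric.** Outcomes {12}, last item: events are monitored actively and passively, and the "total number of events and type of events will be compared between study arms". The light-trap and human-landing outcomes in the same list have negative binomial regression with a cluster random effect. The sections on statistical analysis of the primary and secondary endpoints {20a} give no safety method.
- **Unit of allocation.** Trial design {8}: "A total of 56 clusters will be randomly assigned, in a 1:1 ratio, to one of the two arms", that is, 28 clusters per arm.
- **What is balanced.** Sequence generation {16a}: in each candidate allocation "the differences in treatments allocated between district and land type strata will be assessed". The caption of Appendix Table 2 confirms this: "Only land type and study district were controlled for during random allocation". Household numbers are not a balancing factor.
- **Who holds a device.** Implementation {16c}: "all consented households with a child ≤ 5 years of age will receive a device". Where spares exist, "households without a child" of that age may also get one.
- **Village size.** Appendix Table 1: "Clusters were restricted to those with more than 109 households with children ≤ 5 years of age and no more than 245 total households". Recruitment {15} instead gives more than 150 houses with a young child.

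**The concern.** Equal numbers of villages do not guarantee equal numbers of households. An arm that happens to hold the larger villages, or more of the spare devices, collects more events at the same underlying rate. A difference in totals could then look like harm, or a real difference in rate could be diluted.

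Villages may also differ in how often events occur or are reported. If so, totals vary more than independent counts would.

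Safety is a listed secondary objective, the device runs overnight where young children sleep, and the data safety monitoring board may see unblinded adverse-event data. The comparison should therefore be one that can be interpreted.

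**Working it through.** **The plan's own figure.** None is stated for safety. The design figures come from Sample size {14}: prevalence 20% against 12%, between-cluster CV 0.5, and 100 children per cluster. With the unmatched-cluster formula (two-sided 5%, assumed) they give 27.7 clusters per arm, rounded up to the stated 28. At 60 children, power is 87.2% against the stated 86%. The design is therefore read correctly here. That CV of 0.5 concerns malaria prevalence, not adverse events.

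**Step 1: imbalance in households.** Assume sizes are uniform on the integers from 110 to 245 and that every household holds a device.
- Mean = 177.5. SD = sqrt((136² − 1)/12) = 39.3. CV = 39.3/177.5 = 0.221.
- SD of the log arm ratio ≈ 0.221 × sqrt(2/28) = 0.0591.
- 95% range = exp(±1.96 × 0.0591) = 0.89 to 1.12. Simulation gives the same.

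With sizes uniform on 151 to 245, the mean is 198 and the CV 0.138, and the range is 0.93 to 1.08. In an extreme case, with about half the villages at each of 110 and 245, it is 0.82 to 1.22.

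**Step 2: effect on the ratio of totals.** Ratio of totals = rate ratio × household ratio.
- Equal rates, household ratio 1.12: 1.00 × 1.12 = 1.12, an apparent excess.
- True rate ratio 1.25, household ratio 0.89: 1.25 × 0.89 = 1.11, a diluted excess.

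**Step 3: if totals were tested.** The protocol names no test, so this step is conditional. Take z = (a − b)/sqrt(a + b), where a and b are the event totals in the two arms. Let μ be the mean events per village and k the CV of village event rates. With no true difference, the variance of z is inflated by

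V = 1 + μ × [(1 + 0.221²)(1 + k²) − 1],

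and the rejection rate is 2 × [1 − Φ(1.96/√V)].

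At 0.05 events per household, μ = 177.5 × 0.05 = 8.875:
- k = 0: V = 1 + 8.875 × 0.0489 = 1.43, rejection 10%.
- k = 0.5: V = 1 + 8.875 × 0.311 = 3.76, rejection 31%.

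Results for sizes 110 to 245, with 20,000 simulated null trials per cell agreeing to within about one percentage point:

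| Events per household | Events per arm | k = 0 | k = 0.25 | k = 0.5 |
|---|---|---|---|---|
| 0.01 | 50 | 6% | 7% | 12% |
| 0.02 | 99 | 7% | 10% | 18% |
| 0.05 | 248 | 10% | 17% | 31% |
| 0.10 | 497 | 15% | 26% | 44% |

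With sizes 151 to 245, the rates at 0.01 to 0.05 events per household run from 5% (k = 0) to 31% (k = 0.5). A cluster-level t-test on rates rejects in about 5% of null trials in every cell.

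**Step 4: which part matters.** At 0.05 events per household and k = 0.5, adding the denominator but ignoring cluster still rejects in about 28%. At k = 0 the denominator alone restores 5%. Both parts of the fix are needed if villages vary.

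**The case against.** The strongest reply is that Outcomes {12} is a list in shorthand. It names no test, interval or decision rule for safety, and its wording fits an ordinary table of events by arm and type. Denominators and cluster adjustment are commonly left to the analysis plan, which exists but is not shown. That stands: the missing safety model is not itself an error. What remains is that the list does name the metric, and the metric is totals. Totals from groups of unequal size mislead even in a descriptive table.

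A reader might infer more than the documents support:

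- **That the arms are unbalanced.** The documents show only that balance in household numbers is not enforced. Expected numbers are equal, and any imbalance is by chance.
- **That events cluster by village.** This is plausible, since village health teams make the monthly visits, but it is not stated. Staff are blinded and both arms are visited alike, so differences in reporting would add noise, not a systematic bias.
- **That most null trials would falsely signal harm.** Rejection rates of 60% to 79% do arise, but only at 0.5 to 1 event per household with k of 0.3 to 0.5, and only with a test that nobody has planned. Adverse Event Reporting {22} expects no events from the intervention and gives no background rate.
- **That child households range from 110 to 245.** This joins a floor on child households to a cap on all households, and it sets aside the floor of more than 150 in Recruitment {15}.
- **That a difference in totals would drive decisions.** Clinician review weighs type, frequency and relatedness.

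**Conclusion.** The point holds in a limited form. As written, the between-arm safety metric is a raw total, in a design that neither fixes nor balances the number exposed, so exposure and event rate are mixed. The likely chance distortion is modest: about 11% to 12% either way under the wider size assumption, and about 7% to 8% under the narrower one.

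The false-positive figures of about 5% to 31% are conditional on totals being tested as simple counts, 0.01 to 0.05 events per household, and an adverse-event CV of 0 to 0.5. They rise with more events. None of these inputs is in the documents, nor is the shape of the size distribution or full device coverage. The case for change does not depend on the upper end: a rate is the right quantity for this comparison and costs almost nothing.

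**What to change.** In Outcomes {12}, replace the comparison of totals with:

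1. Adverse events, and serious adverse events separately, per enrolled household-month in each arm. Count time from device distribution to withdrawal or study end. Do not use measured device use: the article mentions only opportunities to check use at monthly visits and reviews to guide retraining, so a complete use record cannot be assumed.
2. The proportion of households, or of children where their number is known, with at least one event.
3. A rate ratio with an interval that allows for cluster. The negative binomial model with a cluster random effect already planned for mosquito counts would serve, with log household-months as offset. If events are few, compare cluster-level rates instead.
4. Totals and event types by arm as description, with the number of device households beside them.

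Two pairs of statements affect the denominator and must be reconciled. Trial design {8} gives a device to all eligible consenting households, while Implementation {16c} gives one to households without a young child only where spares exist. Recruitment {15} and Appendix Table 1 give different floors for child households (more than 150 and more than 109).

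**Cost:** wording, slightly more analysis work, and wider intervals. No change to sample size is needed, and enrolment, distribution and withdrawal records should supply the household-months. The change should be made before the database is locked and the statistician unblinded.

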### Participant timeline {13}

**Table Tabb:** 

Month	Study period				
	Enrolment/Baseline data collection	Intervention			Close out
	0 (June 2024)	6 (Dec 2024)	9 (March 2025)	12 (June 2025)	July–Oct 2025
*Enrolment:*					
Household enrolment	X				
Device distribution	X				
U5 eligibility screen	X				
U5 enrolment	X				
Baseline U5 blood sampling	X				
Household survey	X				
CDC light trapping enrolment	X				
Baseline CDC light trapping	X				
HLC enrolment	X				
Baseline HLCs	X				
Air sampling enrolment			X		
*Intervention:*					
Blood sampling		X		X	
Household survey		X		X	
CDC light trapping		X		X	
HLCs		X		X	
Insecticide resistance sampling				X	
Air sampling			X	X	
Acceptability survey		X		X	
FGDs				X	
*Assessments:*					
Final analysis					X
Dissemination of results within community					X

## Sample size {14}

Data collected from the study region suggest prevalence of malaria infection by RDT in children ≤ 5 years of age is 20%. A conservative coefficient of variation (CV) of 0.5 for between cluster prevalence was assumed. To detect a 40% reduction in prevalence with 90% power, we need 28 clusters per arm and a sample of 100 children in each cluster. Due to budget restrictions, sample size was reduced after baseline to 60 children in each cluster at 6 and 12 months, resulting in 86% power.

Entomological sample sizes were determined based on logistics, considering budget and personnel restrictions. The sample sizes of similar studies were also considered. For CDC light trapping, sampling will be carried out in all clusters and randomised at the household level. HLCs will be randomised at both the cluster and household level.

### Recruitment {15}

Community sensitisation will take place by the study team and VHTs communicating the study purpose and activities and will also involve local leaders. This will be done at multiple levels including centrally at the Ministry of health, district level and the village level. Active recruitment will take place through the provision of information by designated study staff to central points of the community, such as community leaders, health workers, schools and churches. Information will then be further provided to parent(s)/guardian(s) of potential participants through word of mouth to provide potential study participants further information on the study. Clusters have been identified where there are more than 150 houses with a child ≤ 5 years of age, to ensure that the sample size will still be met in the case a proportion of households do not consent to primary endpoint sampling.

## Assignment of interventions: allocation

### Sequence generation {16a}

All randomisation procedures will take place electronically. Treatment and control will be assigned as blinded, variables A and B, by the trial data manager and details of this assignment will be recorded in a sealed envelope and will not be shared with or accessible to any other team members.

The unit of randomisation is a cluster, corresponding approximately to villages within the study area. Clusters will be randomly assigned to two study arms, control and treatment intervention, using a computer-assisted constrained randomisation approach, facilitated by R [19]. To ensure adequate and feasible sampling, cluster selection will be restricted based on population size and population stability (Appendix Table 1). To reduce the impact of confounding factors, clusters will be stratified by land type (urban or rural) and study district, ensuring equal representation across both study arms. No significant inter-cluster variation was identified, meaning household selection within clusters will proceed as simple random sampling without blocking. This randomisation procedure involves generating 1000 unique sets of random treatment assignments. In each cycle, the differences in treatments allocated between district and land type strata will be assessed and the iteration with the least disparity, considered the most well-balanced iteration, will be selected as the final scheme for assigning treatments. Additional confounding factors will be factored into the statistical analysis (Appendix Table 2).

### Concealment mechanism {16b}

Investigators, study staff, statistician and study participants will be blinded to treatment allocation of clusters. The intervention and control will be deployed in houses by blinded study personnel using a blinded coding system. Following completion of the trial and locking of the database, the study statistician will conduct an unblinded analysis.

### Implementation {16c}

The distribution of the intervention will occur immediately following baseline data collection, and thus verification of underlying assumptions of study power (prevalence and CV) will not be verified prior to distribution. Analysis of baseline data will take place prior to the first round of intervention data collection, providing an opportunity to revise sample sizes if necessary. Within a cluster, all consented households with a child ≤ 5 years of age will receive a device regardless of whether they are randomly selected for sampling at the baseline time point. Where spare Mossie-GO™ devices are available, households without a child ≤ 5 years of age will also be given a device. As per the manufacturer’s guidance, the device requires 2 h charging time during the day and should be switched on in the evening and placed in the room with the child ≤ 5 years of age. If multiple children ≤ 5 years of age sleep in different locations, one location should be selected. If there are no children ≤ 5 years of age within the household, the Mossie-GO™ device can be placed in an alternative sleeping room. Trained VHTs and data collectors will be responsible for deployment of the product and monthly refill/disposal of the discs at monthly intervals within the sample populations to ensure adherence. Reviews of device use will be conducted to inform any retraining requirements.

## Assignment of interventions: blinding

### Who will be blinded {17a}

This is a double-blinded trial in which the trial participants and all study staff will be blinded, with the exception of two delegated unblinded study staff members. These include the two members of staff responsible for coordinating the manufacture and distribution of the Mossie-GO™ to either the treatment or control cluster. The data manager who implements the allocation sequence and the statistician responsible for analysis will remain blinded until the completion of data collection and the locking of the database at the end of the study.

### Procedure for unblinding if needed {17b}

Study unblinding will occur in the case of an AE or SAE, at the discretion of the principal investigators (PIs). The site clinician will review all AEs and SAEs and inform the PI of the AE/SAE under consideration within 24 h. If deemed necessary, a delegated unblinded study staff member will determine if the participant and household allocation are within the control or intervention arm. If they are within the intervention arm and deemed necessary by the PI and site clinician after considering the type and frequency of event and reviewing the likelihood of the adverse event to be related to the study, action will be taken such as study termination or device withdrawal until further investigation. All cases of study unblinding will be well documented using an unblinding log and considered within the study analysis, for example, in the case a whole cluster becomes unblinded through participant communication. Documentation of the unblinding will be reported to the data safety monitoring board (DSMB) and international research board (IRB).

